#### Screening/baseline assessment

Potentially eligible and interested volunteers are invited to participate in a screening and baseline assessment appointment. This appointment takes approximately three hours. A trained research staff member obtains informed written consent. Participants complete online questionnaires via REDCap to assess social functioning, perceived stress, depression symptoms, and eating behaviors. A project staff member administers a structured clinical interview to rule out the presence of a psychiatric disorder, current self-injurious behavior, or current suicidal behavior that would warrant more intensive treatment. Participants who meet criteria for a current full-syndrome psychiatric disorder or who report current and active suicidal ideation are immediately referred to CAMP behavioral health staff for further evaluation and treatment. At the screening visit, project staff also administer a semi-structured interview to assess eating patterns, including overeating and binge eating, and review a 3-day diet record. Research staff who administer clinical interviews are trained by clinical psychologists through a combination of didactics, role-playing, and live supervision. Clinical interviews are audio-recorded and reviewed by clinical psychologists on the research team for fidelity to the interview protocol. At the end of the screening visit, participants are fitted with an ambulatory accelerometer that they are asked to wear for seven days following the study visit to measure habitual physical activity. Participants are paid $50 for completing this screening visit. At the end of the screening visit, eligible participants are randomized to either IPT + usual care or usual care only.

#### Mid-program assessment

Participants complete a brief assessment, estimated to take no longer than 30 min, halfway through the experimental phase, corresponding to about 6–9 weeks after the baseline assessment. Participants repeat questionnaires assessing social functioning, stress, depression symptoms, and eating behaviors. They also re-wear the accelerometer for seven days following the study visit to re-assess habitual physical activity. Participants receive a pack of newborn diapers for completing this mid-program assessment.

#### Post-program assessment

Participants complete an assessment at the end of the experimental phase, which corresponds to about 12–18 weeks after the baseline assessment and just prior to delivery. This assessment takes about two hours. Participants repeat the same research tasks as at the baseline assessment. In addition, a project staff member administers a program acceptability interview to adolescents who were randomized to the IPT condition. Participants are paid $75 for completing the post-program assessment.

#### 3-month postpartum assessment

Participants complete a final assessment at 3-months postpartum, a time when inter-individual differences in postpartum weight retention and postpartum depression emerge [92]. Participants repeat the same research tasks at the baseline assessment. Participants’ 3-month old babies complete an infant body composition assessment using air displacement plethysmography (PEAPOD). A project staff member reviews the medical record to assess measured height and weight at delivery and postpartum appointments, as well as any pregnancy or birth complications. Participants are paid $75 for completing the 3-month postpartum assessment.

Participants are invited to opt in, or out, of an additional adjunct metabolic study, which includes a maternal DXA scan of post-partum adiposity and a 2-h oral glucose tolerance test (OGTT) to estimate maternal post-partum insulin sensitivity. Participants are paid $75 for the adjunct metabolic procedures.

### Sample size

We plan to randomize 50 out of 80 (60%) enrolled participants following a screening/baseline eligibility assessment. Our estimation of a total sample size of *N* = 50 (i.e., *n* = 25 per condition) is based on recommendations for a two-arm superiority pilot trail in which small-to-moderate standardized effects are anticipated [93]. Furthermore, our sample size estimation is consistent with recommendations for pilot randomized trials using an 80% one-sided confidence interval approach to exclude a clinically important difference between study arms [94].

### Statistical analysis

Baseline participant characteristics and feasibility/acceptability findings will primarily be measured with descriptive statistics, including mean with standard deviation, median with interquartile range, frequency, and percentage. Analysis of covariance (ANCOVA) will be used to evaluate group differences (IPT + usual care versus usual care) in secondary outcomes, including social functioning, perceived stress, depression symptoms, eating behaviors, physical activity, sleep disturbance, maternal post-partum insulin sensitivity, maternal post-partum adiposity, and infant adiposity. We will use 95% confidence intervals to measure precision of the estimated differences between conditions, per recommendations [95]. Given that this is a pilot study, results will be considered preliminary. Although our theoretical framework suggests that IPT + usual care, as compared to usual care only, will impact these secondary outcomes via a series of mechanistic pathways, this pilot feasibility study is not sufficiently powered to test mediation. Covariates considered in these models will include baseline maternal age, gestational age, race/ethnicity, baseline CES-D score, and pre-pregnancy BMI/weight status. Missing data will be examined for patterns of missingness and imputation, with the intent-to-treat sample, will be used if deemed appropriate. Given the pilot nature of the study, we also will conduct sensitivity analyses using listwise deletion with complete data.

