### Outcomes

Primary and secondary outcomes are summarized in Table 2.

**Table 2 Tab2:** Overview of constructs and assessments throughout the randomized controlled pilot study protocol

Construct	Measurement	Description	Intervals assessed	Reference
Primary outcomes				
Feasibility of study		Number of eligible participants, randomized participants, retention and attrition of randomized participants	Baseline, mid-pregnancy, post-program, 3-month postpartum	[65]
Acceptability of IPT		IPT session attendance (≥ 80%), above-average participant IPT program ratings	Post-program	[66]
Secondary Outcomes				
Social functioning	SAS-SR	24-item self-report scale of interpersonal functioning in family, friend, romantic, and school or work domains	Baseline, mid-pregnancy, post-program, 3-month postpartum	[67]
	NRI-BSV	28-item self-report scale of relationship characteristics for mother, father, peer, and romantic partner relationships		[68]
Perceived stress	PSS	14-item self-report scale to assess perception of stress	Baseline, mid-pregnancy, post-program, 3-month postpartum	[69]
Depression	CES-D	20-item self-report scale to assess depression symptoms	Baseline, mid-pregnancy, post-program, 3-month postpartum	[70]
	EPDS	10-item self-report scale to assess depression symptoms	Baseline, mid-pregnancy, post-program, 3-month postpartum	[71, 72]
	MINI-KID	Structured clinical interview to assess psychiatric disorders, such as major depressive disorder	Baseline, post-program, 3-month postpartum	[73]
Disinhibited eating	EDE	Semi-structured interview to assess disordered eating including objective binge, subjective binge, and objective overeating	Baseline, post-program, 3-month postpartum	[74, 75]
	EES-C	25-item self-report questionnaire to assess eating in response to negative emotions	Baseline, mid-pregnancy, post-program, 3-month postpartum	[76]
Physical activity	ActiGraph GT3X+	Body-worn accelerometer to measure 7 days and nights of habitual physical activity including step counts, light and moderate-vigorous intensity, and sedentary time	Baseline, mid-pregnancy, post-program	[77, 78]
Sleep disturbance	ActiGraph GT3X+	Body-worn accelerometer to measure 7 nights of sleep including total sleep time, sleep onset latency, wake after sleep onset, and sleep efficiency	Baseline, mid-pregnancy, post-program	[79, 80]
Body composition	BMI indices	Height and weight measured to calculate BMI	Baseline, mid-pregnancy, post-program, 3-month postpartum	[81]

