We considered the selection of the control group extensively. A limitation of our usual care control is that we will not be able to account for potential confounding effects of attention. Because adolescent patients receive education about depression as part of prenatal usual care, and because we seek to first establish feasibility and acceptability, we felt that comparison to usual care was the optimal, initial step. Depending upon the results, a subsequent well-powered trial might include a 3-group design comparing [1] IPT to [2] usual care and either (3a) an attention-matched educational control or (3b) a standard behavioral lifestyle intervention. Due to the pilot nature of this study, one shortcoming is that we will only have maternal insulin sensitivity and maternal/infant adiposity at postpartum, and thus, will not be able to control for earlier levels of these variables. These measures are secondary outcomes, and if positive signals are detected from these pilot data, future studies might consider use of repeated measures of maternal metabolic characteristics and measures at birth of infant adiposity. Another limitation of this pilot study is that outcome assessors are not blind to intervention assignment, and thus, assessment of some outcomes may be influenced by expectancy biases (i.e., such as those measured by clinical interview). That being said, a potential strength of the current study is heterogeneity of outcome variables, either by participant self-report or objective measures, such as accelerometers to assess habitual physical activity and sleep. A subsequent randomized controlled effectiveness trial would have the resources to ensure that research study staff who collect outcome data are blind to intervention assignment.

The concept of focusing on pregnant adolescents will allow us to target an underrepresented, underserved group who are likely to face heightened social-emotional challenges as compared to pregnant adult women [35]. Opportunities to intervene with this at-risk group can be expected to help prevent many of these young women, and their future infants, from a lifetime trajectory of obesity with its multiple adverse health consequences. The proposed IPT intervention represents a novel approach to addressing excess GWG in adolescents by targeting psychosocial risk factors including social functioning, perceived stress, and depression symptoms.

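### Apart from CES-D, the ANCOVA covariate list names no outcome's own baseline value, at some cost in precision for secondary outcomes measured before randomization

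*Protocol article*

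**What the plan says.** The Statistical analysis section of the protocol article sets the method: "Analysis of covariance (ANCOVA) will be used to evaluate group differences (IPT + usual care versus usual care) in secondary outcomes". It then names nine outcome groups: social functioning, stress, depression, eating, physical activity, sleep, maternal insulin sensitivity, maternal adiposity and infant adiposity. Precision is to be judged by interval: "We will use 95% confidence intervals to measure precision of the estimated differences between conditions". One covariate sentence serves all of these models: "Covariates considered in these models will include baseline maternal age, gestational age, race/ethnicity, baseline CES-D score, and pre-pregnancy BMI/weight status".

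Table 2 (Outcomes) schedules the social functioning, stress, depression and emotional-eating questionnaires at "Baseline, mid-pregnancy, post-program, 3-month postpartum". The EDE interview is also scheduled at baseline. The Screening/baseline assessment section confirms this: "Participants complete online questionnaires via REDCap to assess social functioning, perceived stress, depression symptoms, and eating behaviors". The eating interview takes place at the same visit. Allocation comes last: "At the end of the screening visit, eligible participants are randomized to either IPT + usual care or usual care only". The activity monitor is different. Participants leave that visit with an "ambulatory accelerometer that they are asked to wear for seven days following the study visit to measure habitual physical activity".

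The Discussion counts it as a shortcoming that insulin sensitivity and adiposity are measured only postpartum, so that the authors "will not be able to control for earlier levels of these variables".

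**The concern.** In an ANCOVA of a repeatedly measured scale, the outcome's own pre-randomization value is usually the most useful covariate. The printed list contains that value for CES-D only. Taken as written, a PSS model would adjust for baseline CES-D but not for baseline PSS. The same holds for SAS-SR, NRI-BSV, EPDS, EDE and EES-C.

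The Discussion regrets the lack of such control where it is impossible, but the Statistical analysis section does not state it where it is possible. The secondary aim is to estimate effects. The Sample size section expects only small-to-moderate effects and plans 25 participants per arm, so the width of the intervals matters to what can be learned.

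**Working it through.** **Which outcomes are affected.** Of the nine ANCOVA groups, six have a scheduled baseline. Physical activity and sleep drop out because their recording week comes after the visit at whose end allocation occurs. Four groups remain with a clean pre-randomization value: social functioning, stress, depression and eating. Depression is already partly covered, because baseline CES-D is listed.

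**Inputs.** 50 randomized, 25 per arm (Sample size). The retention target is 38 of 50 (Feasibility of study), taken here as 19 per arm on the assumption of even loss. The documents give no SD and no correlation, so there is no stated precision figure to reproduce. N = 50 rests on cited pilot-trial recommendations and is not disputed here. The correlation r is an assumption. It is the partial correlation of own baseline with follow-up, given the five listed covariates.

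**Formula.** In units of the residual SD after the listed covariates, with n per arm:

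- without own baseline: half-width = t(0.975, N − 2 − 5) × √(2/n)
- with own baseline: half-width = t(0.975, N − 2 − 6) × √(2(1 − r²)/n)

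Each listed covariate is counted as one term.

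**N = 50.** Without own baseline: 2.017 × √(2/25) = 2.017 × 0.2828 = 0.570. With it, for example at r = 0.5: 2.018 × 0.2828 × √0.75 = 0.494.

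| Assumed r | Residual variance removed | Half-width, N = 50 (0.570 without) | Half-width, N = 38 (0.662 without) |
|---|---|---|---|
| 0 | 0% | 0.571 | 0.663 |
| 0.3 | 9% | 0.545 | 0.632 |
| 0.5 | 25% | 0.494 | 0.574 |
| 0.7 | 49% | 0.408 | 0.473 |

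**Allowing for chance imbalance in the covariates.** Multiplying the variance by about (N − 3)/(N − k − 3) for k covariates, the ratio of half-widths at N = 50 is 1.013, 0.966, 0.877 and 0.723 for r = 0, 0.3, 0.5 and 0.7. That is a widening of about 1.3%, then narrowings of about 3%, 12% and 28%. At N = 38 and r = 0 the widening is about 1.8%. Break-even lies between about r = 0.15 and r = 0.20.

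**In participants.** N/(1 − r²) at N = 50 gives about 55, 67 and 98 for r = 0.3, 0.5 and 0.7.

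**Why r must be partial.** Baseline CES-D already does some of the work. Suppose own baseline correlates 0.6 with follow-up and 0.5 with baseline CES-D, and CES-D relates to follow-up only through own baseline, giving 0.6 × 0.5 = 0.30. The partial correlation is then (0.6 − 0.30 × 0.5)/√((1 − 0.09)(1 − 0.25)) = 0.45/0.826 = 0.545. The further variance reduction is about 30%, where the crude 0.6² would suggest 36%.

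**The case against.** The strongest reply is that nothing has been decided against baseline adjustment. The covariates are described as *considered* and as what the models *will include*, which does not close the list. The Discussion sentence on metabolic measures makes most sense if earlier levels are controlled for wherever they exist. A journal article also condenses a fuller protocol, and model terms for each outcome can be left to an analysis plan. This stands to the extent that a deliberate omission cannot be claimed. It does not remove the point. The article chose to print a specific list, down to one named outcome baseline, and no section states the own-baseline term for the others. Whether the list is open or closed, the same sentence is needed.

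A second reply is that the gain may be small. Baseline is at 12–18 weeks gestation and the last assessment at about 12 weeks postpartum, so a modest correlation is plausible. Randomization is stratified by CES-D level, weight status, age and race, and baseline CES-D is a covariate, so imbalance in related scales is partly handled. That also stands, and it is why low values of r are shown.

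A reader might infer that the estimates are biased, or that the larger trial's planning is compromised. The documents support neither. Allocation is random, and the Discussion says that feasibility and acceptability findings will inform the larger trial, giving secondary signals only a looser role. The primary outcomes are descriptive and unaffected.

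**Conclusion.** The point holds as one of precision and clarity. For SAS-SR, NRI-BSV, PSS, EPDS, EDE and EES-C, a pre-randomization value is collected but not named in the model. At N = 50 the 95% half-width of about 0.57 SD would become about 0.55, 0.49 or 0.41 SD if the partial correlation were 0.3, 0.5 or 0.7. These correlations are assumptions, and the SD is the residual SD after the listed covariates.

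It is tempting to call the adjustment free. It nearly is, but it uses one degree of freedom, and below a correlation of about 0.15 to 0.20 it widens the interval slightly. It is also tempting to extend the point to every outcome with a baseline row in Table 2. That fails for CES-D, which is already listed, and for the accelerometer measures, whose first week is recorded after allocation.

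**What to change.** Add one sentence to the Statistical analysis section: each ANCOVA for an outcome measured before randomization includes that outcome's baseline value, in addition to the covariates already listed. Gestational age and the stratification factors (age, weight status, race/ethnicity and baseline CES-D) stay in the model. For outcomes measured only postpartum, keep the present list. Do not use the first accelerometer week as a covariate for physical activity or sleep while it is recorded after allocation, since it could already reflect the assigned arm.

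The change needs no new data, visits or participants. It costs a line of wording and one degree of freedom per affected model.

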### Ethics and dissemination

The protocol has been approved by a single Institutional Review Board, the Colorado Multiple Institutional Review Board (COMIRB), which provides oversight for the University of Colorado School Of Medicine and Children’s Hospital Colorado. An Institutional Review Board authorization agreement was established between the Institutional Review Board of Colorado State University, an administrative site, and COMIRB, in order for COMIRB to serve as the primary IRB. We follow Institutional Review Board requirements pertaining to reporting of unanticipated problems and adverse events.

Personal information is collected directly from research participants and from their medical record. Personal information is stored separately from other research data and will not be shared with anyone outside of the research team, which includes personnel at the University of Colorado, Children’s Hospital Colorado, and Colorado State University, with the exception of entities that monitor human subject research, such as COMIRB. Electronic data are stored and managed by REDCap and a secure server at the University of Colorado. The REDCap system is password protected and only accessible by research staff members. Digital audio recordings from interviews and interventions are uploaded to password-protected folders on a secure server at the University of Colorado. After uploading, recordings are deleted from the digital recording device. Paper data are stored in locked cabinets in administrative research space at Children’s Hospital Colorado. All data will be preserved for seven years following IRB acknowledgement of study closure. Results and conclusions from the current study will be disseminated by publication in peer-reviewed journals and conference presentations. We also will disseminate findings to clinic providers who have been involved in supporting the study.

## Discussion

The current study is a randomized controlled feasibility study piloting a novel approach to the prevention of excess GWG in adolescent pregnancy. The primary aim is to assess the feasibility and acceptability of a relatively brief, 6-session individual IPT program, delivered within the context of an interdisciplinary adolescent pregnancy hospital clinic. The secondary aim is to explore whether there are health benefits to pregnant adolescents who receive IPT—in perinatal social functioning, perceived stress, depression symptoms, eating behaviors, physical activity, sleep, GWG, and postpartum maternal and infant metabolic health—as compared to the usual care that pregnant adolescents would receive in an interdisciplinary adolescent maternity clinic.

Preventative interventions for excess GWG in adult women have previously focused on lifestyle modification, including healthy eating and physical activity. The available literature suggests that lifestyle-based interventions require significant financial and time resources, and unfortunately, generally demonstrate insufficient effectiveness [29]. Moreover, no study to date has been specifically designed to evaluate a prevention of GWG intervention in pregnant adolescents, even though excess GWG is prevalent in this population and is associated with serious, negative health outcomes [3]. Pregnant adolescents face unique socioemotional needs, often including mental health problems, academic problems, family conflict, and poverty [35]. There is growing evidence that such social-emotional factors may interfere with a healthy weight gain in pregnancy through their influence on overeating to cope with negative emotions and stress, reduced physical activity, and disturbed sleep [96, 97]. From an interpersonal theoretical framework, receipt of an IPT intervention is posited to reduce conflict and increase support in adolescents’ interpersonal relationships, which in turn, is theorized to improve perceived stress and negative affect, and ultimately facilitate healthy eating, physical activity, and sleep to influence a healthy GWG.

The proposed pilot randomized feasibility study is the first necessary step in understanding the potential utility of an evidence-based psychotherapy intervention—addressing social functioning, stress, and negative emotions—for prevention of excess GWG in adolescent pregnancy. We anticipate that IPT will be feasible and acceptable to pregnant adolescents. Moreover, we have preliminary data that suggest it will be feasible to incorporate a psychosocial intervention into an interdisciplinary hospital clinic, as evidenced by a 72% attendance rate in an existing parenting skills training intervention in the CAMP clinic. However, it is possible that there could be obstacles to attendance (e.g., transportation). Some we have anticipated (e.g., providing taxis and bus passes as needed), but others (e.g., school/work schedules) could interfere with sessions. A strength of the individualized nature of our IPT program is that it permits a high degree of flexibility in rescheduling sessions at alternative times.

With respect to secondary outcomes, we anticipate that adolescents who receive IPT, relative to usual care only, will show patterns of improved perinatal social functioning, lower perceived stress, reduced depression symptoms, healthier eating patterns, increased physical activity, improved sleep, less excess GWG, and better postpartum maternal and infant metabolic health. However, IPT may improve social-emotional adjustment without preventing excess GWG or postpartum weight retention and metabolic outcomes. In this case, we would have initial evidence for a brief, potentially cost-effective approach to improving social-emotional health in pregnant adolescents, which has important public health relevance for postpartum depression prevention and maternal-infant health, given the serious, negative effects of depression on maternal-infant psychosocial outcomes [98]. Ultimately, results and conclusions have the potential to benefit not only emotional and physical health outcomes for adolescent mothers, but also health outcomes for offspring as part of a larger public health perspective on the intergenerational transmission of depression, obesity, and cardiometabolic disease.

Feasibility and acceptability findings from the current pilot study will inform the development of a larger randomized controlled trial that is adequately powered to measure the effectiveness of this brief individual psychosocial intervention to prevent excess GWG in adolescents. Testing the effectiveness of this psychosocial intervention within the structure of an existing interdisciplinary adolescent maternity hospital clinic is ideal to facilitate successful transfer of research-based knowledge to routine clinical practice. The potential for dissemination of this psychosocial intervention is further enhanced by evidence showing that IPT can be delivered effectively and with fidelity by trained facilitators who do not necessarily have an advanced degree in psychology, such as lay community health workers [99].

We considered the selection of the control group extensively. A limitation of our usual care control is that we will not be able to account for potential confounding effects of attention. Because adolescent patients receive education about depression as part of prenatal usual care, and because we seek to first establish feasibility and acceptability, we felt that comparison to usual care was the optimal, initial step. Depending upon the results, a subsequent well-powered trial might include a 3-group design comparing [1] IPT to [2] usual care and either (3a) an attention-matched educational control or (3b) a standard behavioral lifestyle intervention. Due to the pilot nature of this study, one shortcoming is that we will only have maternal insulin sensitivity and maternal/infant adiposity at postpartum, and thus, will not be able to control for earlier levels of these variables. These measures are secondary outcomes, and if positive signals are detected from these pilot data, future studies might consider use of repeated measures of maternal metabolic characteristics and measures at birth of infant adiposity. Another limitation of this pilot study is that outcome assessors are not blind to intervention assignment, and thus, assessment of some outcomes may be influenced by expectancy biases (i.e., such as those measured by clinical interview). That being said, a potential strength of the current study is heterogeneity of outcome variables, either by participant self-report or objective measures, such as accelerometers to assess habitual physical activity and sleep. A subsequent randomized controlled effectiveness trial would have the resources to ensure that research study staff who collect outcome data are blind to intervention assignment.

The concept of focusing on pregnant adolescents will allow us to target an underrepresented, underserved group who are likely to face heightened social-emotional challenges as compared to pregnant adult women [35]. Opportunities to intervene with this at-risk group can be expected to help prevent many of these young women, and their future infants, from a lifetime trajectory of obesity with its multiple adverse health consequences. The proposed IPT intervention represents a novel approach to addressing excess GWG in adolescents by targeting psychosocial risk factors including social functioning, perceived stress, and depression symptoms.

